**DATE: 04/26/12**

## **I. BACKGROUND AND SIGNIFICANCE**

The experience of pain has both sensory and affective elements, and can be modulated with cognitive distractions as well as emotional manipulation. The neural network involved in analgesia includes both the dopaminergic reward system and a descending pain inhibitory opiodergic system that begins in the cerebral cortex and extends downwards to the spinal cord, with some evidence of additional mediators that antagonize the opiodergic circuit through factors such as anxiety. Placebo analgesia studies have shown an effect from verbal expectancy manipulation, which can be additionally boosted through covert conditioning. More recently, there have been a number of demonstrations of music’s analgesic capabilities in experimental settings1,2,3,4,5. Music has been shown to both reduce anxiety and activate reward circuitry6,7; because both factors are part of the neural pathways modulating pain perception, it is possible for music to access one or both pathways as an analgesic vehicle.

In this study, we propose to control or measure all previously successful elements of music analgesia. Following the success and feasibility of the personal music choice paradigm in healthy subjects (protocol 2010P002894) and of conditioning (protocols 2011P000748, 2009P000096, 2004P000096), here we implement both for pain experience, which has mind and body components. We intend to harness the potential benefit of familiarity to enhance music analgesia, and will also further the clinical promise of this intervention by using conditioning to augment any effects that music has on pain perception.

**The use of personal music choice in music induced analgesia**

Applied to pain-related disorders, music as a therapeutic modality has a number of advantages over more traditional therapies. Pathologies like depression, often associated with long term illnesses like chronic pain, tend to manifest with different symptoms across cultures8, making it difficult to address ethnically and demographically diverse groups with psychotherapy. In the US, the probability of two people of different ethnicities being selected when picked randomly from the country is about 50%. Music has the power to universally be understood: even a culture that has never heard a note of Western music can understand its basic emotionality9. It is also becoming highly accessible through services like Pandora Radio and YouTube (both free with Internet access). We know that it can have a strong effect across a variety of people, as even musically untrained (experience only through everyday exposure) listeners can still have strong emotional responses10. Perhaps most importantly, music is highly socially accepted, whereas psychotherapy and medication carry much stigma, leading to decreased adherence and possibly even delay or prevented initiation of treatment. Lastly, in contrast to many medications, using music is low risk and has general health benefits11, is of lower cost, and is safe, with no drug interactions.

The scientific complexity of personal music choice is great in the context of analgesia. From the effects of choice4,12, expectation of relief12,13, and potential conditioning from previous exposure14,15, to music specific elements including valence/arousal16,17, mood dependent preferences, specific memories18, and induced chills19, the mechanisms operating behind this potentially powerful clinical tool are many. The neural basis of music and emotions is a nascent yet fast growing area of research, and many overlapping regions between pain and music affective circuitry have been found, including limbic, paralimbic, dopaminergic, and hippocampal networks7. The history of audioanalgesia itself stretches back to 1959, when Gardner20 treated 1000 dental patients and found that using music and noise, ¼ of them did not need any other analgesia during a dental procedure. Through the research proposed in this study, we expect to further increase mechanistic understanding of personal music’s role as a potential analgesic by controlling many of the above factors and testing personal music’s effects in combination with conditioning.

Specifically, we will both verbally induce and measure expectancy of analgesia for their personal music choice. We will also attempt to assess levels of attention and focus on the audio using both scales and interview methods. Balancing carefully between clinical utility and scientific integrity, we are choosing to exclude music choices that invoke specific autobiographical memories and chills, and include a set of individually-selected and characterized songs that are perceived to be highly pleasurable over a range of arousal levels. We will allow individuals to choose their preferred song from that set during the experiment. By requesting that subjects provide songs that cover a range in arousal, we can further explore the uncertainty behind music’s role as a mediator of anxiety or agent of reward2,3,5,16,, as higher arousal is generally correlated with anxiety but higher *music*-induced arousal to strongly pleasurable music is correlated with reward. Roy et al (2012) specifically tested arousal to pleasant music for pain modulation, but their samples were not personally chosen by the subjects, and other studies have shown familiarity to mediate reward in the context of arousal14. Lastly, conditioning has clearly been able to enhance the analgesic effects of paired stimuli. Because the neurophysiological mechanisms of the effects of music on pain are still largely unclear, the interaction between conditioning and the music element may yield additional insight about the cognitive and affective aspects of music analgesia.

**Experimental manipulations of expectancy**

Positive expectation of pain relief is likely a critical component of context effects in pain treatments, but one that is challenging to tease out from other context effects and manipulate experimentally. Additionally, a problem with studying analgesia using healthy volunteers in experimentally-induced pain studies is that the analgesic effects can be fewer and of lower magnitude than in genuine clinical pain studies21,22. This study will take advantage of the fact that positive expectation of treatment related to pain relief can be robustly manipulated in an acute experimental setting using a well-studied conditioning- expectancy paradigm23-26. We propose using an experimental manipulation based on the method originally developed by Voudoris and colleagues23, who applied a placebo cream as a local analgesic and surreptitiously reduced the pain stimulus. This manipulation successfully produced heightened analgesia to subsequent noxious stimuli. Here, instead of pairing pain reduction with a physical, inert “analgesic” agent, we will pair it with an emotional and cognitive stimulus (music) that has already shown some analgesic effects on its own (see above). As shown before24, expectancy and conditioning each have separate importance in the context of analgesia, and we will be able to partially differentiate those effects between our conditioning groups and our non-conditioning group. In all published attempts this conditioning paradigm has been effective in creating robust placebo analgesia sufficient to allow quantitative behavioral measurements; in this study we expect the paradigm to robustly boost whatever analgesic effects the personal music stimulus already has.

**Potential clinical applications**

Though music and conditioning have been studied separately as potential mediators of pain relief, they have not to date been combined in a rigorous, controlled study to test their efficacy together. The studies mentioned thus far have found mostly modest effect sizes, but together these two analgesic methods may be able to more substantially reduce pain. In the case that the effects are not linearly additive, the addition of music into the conditioning-expectancy paradigm links a clinically effective, analgesic perceptual modulation with a modality that is already well integrated into most patient’s lives. Additionally, as music is already a medium that induces associative conditioning of socio-cultural cues, emotions, memories, and identity7,18, it may be an ideal candidate for a surreptitiously conditioned analgesic therapy. Piloting of this dual analgesic paves the way to future longitudinal studies of a personal music treatment that is low cost, patient-centered and driven, and can potentially be a lasting, effective relief. This would reduce medication needed and number of medical visits, outcomes that could impact analgesic quantities used post-surgery and by chronic pain patients, and generally decrease the lifestyle impacts that the experience of pain carries with it.

**II. SPECIFIC AIMS**

Music and conditioning to simple cues (e.g light) have each separately shown analgesic effects in experimental pain settings. The goal of this behavioral study is to combine conditioning with both personal music and a control sound sample to test the analgesic effects of these components in healthy subjects.

We expect both conditioning and personal music to have analgesic effects, and that conditioning will further increase the analgesic effects of personal music. To assess the magnitude and specific advantages of music as an analgesic and its potential when paired with conditioning, we will include conditioned chosen sound, non-conditioned chosen sound, and silence as controls in our experiment. The control sound sample serves the important role of controlling for the auditory stimulus modality that music is. In providing a *choice* of sound, our aim is to match the psychological advantages of perceived control, and more strictly test personal music against a relatively innocuous, personally chosen sound.

***Specific Aim****:* This study will combine, separately, specific personal music and chosen sound with conditioning to test whether there are increased conditioning benefits for music vs. sound analgesia on experimental pain in healthy subjects.

***Hypothesis 1****: Highly pleasurable, personally chosen music will reduce pain compared to chosen sound and silence in healthy subjects.*

***Hypothesis 2****: Conditioning will enhance pain reduction when chosen sound or music is on, compared to non-conditioned chosen sound and music.*

***Hypothesis 3****: Conditioning will enhance pain reduction when highly pleasurable, personally chosen music is on, compared to conditioned sound.*

## **III. SUBJECT SELECTION**

In accordance with NIH guidelines, efforts will be made to attain a mix of study participants, in terms of gender and racial/ethnic representation that is reflective of the population of the greater metropolitan Boston area; 63% white, 26% African American and 11% other. Specifically we anticipate that half of our subjects will be male and the other half female and that we will have representation from Asian American, African American and Hispanic minority groups in our final cohorts.

The study will not recruit children under 18 years into this study for several reasons. First there is not sufficient data collected in children documenting the behavioral responses to pain stimuli, or to expectancy manipulations. Second, children may have difficulty understanding and completing the psychometric scales, and struggle with experiencing and rating the pain stimuli.

Inclusion Criteria:

a) Healthy male and female adults aged 18-50

b) Body Mass Index < 30

Exclusion Criteria:

a) Current major medical, neurological, or psychiatric disease

b) Pregnancy

c) Advanced music training

d) Instability of responses to experimental pain (see Study Procedures Section)

e) Non-fluent speaker of English

f) BDI-II (Beck Depression Inventory) score greater than 13

g) Previous experience in pain experiments

h) Current or previous ear/nose/throat or hearing issues compromising ability to listen to audio stimuli

## **IV. SUBJECT RECRUITMENT**

Normal adult volunteers will be recruited by advertising for this study by email, web, and bulletin board announcements posted within/outside the hospital network community according to the protocols approved by the Partners Human Research Committee of Massachusetts General Hospital. All advertisement will be made in accordance with official Internal Review Board policies and constraints. It is not anticipated that additional efforts to recruit minority or female subjects will be required. In addition, the online recruitment system of the MIT Behavioral Research Lab may be utilized as specified in protocol 2010P002894/3. Information to be included in the recruitment notices has been included in this protocol submission.

We will recruit up to 45 subjects or until 36 subjects have completed the study, anticipating an approximately 25% attrition rate for subjects due to inability to meet all continuation requirements (primarily the requirement of stable and reliable responses to pain stimuli necessary to perform the quantitative experiments, as observed in our past and current studies using these methods). All subjects will undergo a telephone or online screening to attempt to distinguish potential subjects from those not meeting eligibility criteria.

During the first visit, one of the study investigators will review all study procedures to be sure subjects are aware of and in agreement with participating in the complete experiment. Written informed consent will be obtained from subjects after all study procedures are described.

Once subjects have met all inclusion criteria, including demonstrated ability to perform the pain rating tasks, they will be randomized into one of three treatment groups – music conditioning, sound conditioning, or routine calibration only.

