## **V. STUDY PROCEDURES**

**Overview of Experimental Design**

To accomplish the Specific Aims, a single two-session experiment will be performed with 36 healthy, pain experiment-naïve subjects who will be randomized into 3 treatment groups. The three treatment groups are music conditioning, sound conditioning, and no-treatment routine pain calibration. Primary outcome measures will include the difference (pre- minus post-treatment) in subjective pain rating to calibrated experimental noxious heat stimuli. We will also collect treatment expectations using an Expectancy of Relief Scale (ERS, below) and ratings of subjective responses to treatments assessed through various psychometric scales and surveys for all groups.

The two behavioral sessions will be separated by a minimum of 2 days and a maximum of 10 days. Subjects will be asked to hold common daily activities constant on experiment days (i.e. duration of sleep, eating habits, caffeine intake). Prior to coming to the experimental site, all subjects will be asked to acquire/choose a set of personal music that satisfies certain criteria for the study (see following section). During both sessions, subjects will be receiving sets of calibrated noxious thermal stimuli and after each stimulus will use 0-100 visual analog scales to rate the pain sensation. In the ***first session***, subjects will go through the consent process and screening questions, and we will also determine whether a subject can report consistent, appropriate responses to the application of the calibrated noxious thermal stimuli. This session will last about 120-150 minutes. In the ***second session*** we will repeat testing for appropriate responses to the thermal stimuli – only subjects that perform consistently on the pain rating task (can reliably rate mild intensity pain stimuli as less painful than moderate intensity stimuli and have comparable ratings across sessions - within 1 STD) will continue to further testing during the second session. Subjects who are eligible to continue will be randomized into one of the three treatment groups (N=12/group). These subjects will then receive a modification of a well-characterized conditioning-expectancy manipulation procedure designed to enhance a subject’s expectation of pain relief in response to their assigned treatment. This session will last about 150-180 minutes. At the end of the study all subjects will be de-briefed so that they understand the procedures and why they were used.

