## **VI. BIOSTATISTICAL ANALYSIS**

**Power Analysis:**
We will study 12 subjects in three groups for a total of 36 subjects; the primary end points are differences between the music/sound conditioning groups and the no conditioning group. In our previous studies for placebo analgesia using a similar model22, 35-37, we observed a SD for pain rating difference of 1.7.  Using this value, with n=12 subjects in each group, we expect 80% power to detect an absolute difference in pain ratings of 2.1 or greater (two sample t-test at the 0.05 two-tailed significance level).

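### Section IV's three recruitment figures do not agree: 45 recruits at about 25% attrition give about 34 completers, not 36 (a minor arithmetic slip with little effect on power)

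*Protocol*

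**What the plan says.** Protocol section IV (Subject Recruitment) gives a recruitment limit, a completion target and an attrition rate in one sentence: "We will recruit up to 45 subjects or until 36 subjects have completed the study, anticipating an approximately 25% attrition rate". It ties that rate to a cause: "anticipating an approximately 25% attrition rate for subjects due to inability to meet all continuation requirements". The same sentence attributes the losses mainly to unstable or unreliable pain ratings and says the rate comes from the group's own past and current studies.

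The target of 36 is the design size elsewhere. Section V (Overview of Experimental Design) plans the experiment for 36 people and says "Subjects who are eligible to continue will be randomized into one of the three treatment groups (N=12/group"). The Session 2 description repeats 12 per group. Section VI (Power Analysis) begins "We will study 12 subjects in three groups for a total of 36 subjects" and rests its power statement on that number: "we observed a SD for pain rating difference of 1.7", and with 12 per group "we expect 80% power to detect an absolute difference in pain ratings of 2.1 or greater", by a two-sample t-test at two-sided 0.05.

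The protocol has no provision for replacing lost subjects or for recruiting beyond 45.

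**The concern.** An attrition rate is a share of the people who start. The number to recruit is therefore the target divided by the retention rate. The stated cap is instead the target multiplied by 1.25, which applies the 25% to completers and not to recruits. The nine extra people are 25% of 36 but only 20% of 45.

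What is at stake is the planned size. If the cap binds and the stated attrition occurs, recruitment ends with fewer than 12 per group, while sections V and VI describe the study as having 12 per group.

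**Working it through.** **Inputs.** Cap 45, target 36 and attrition about 25% (section IV). Group size 12 in each of three groups (sections V and VI). SD 1.7, difference 2.1, power 80%, two-sided alpha 0.05, two-sample t-test (section VI).

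**1. Reproducing the cap.**
- Target / (1 - attrition) = 36 / 0.75 = 48. This is not the stated figure.
- Target x (1 + attrition) = 36 x 1.25 = 45. This matches exactly.
- Attrition at which 45 recruits give 36 on average: 1 - 36/45 = 20%.

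**2. Expected completers from 45.** Formula: 45 x (1 - attrition).

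| Attrition | Expected completers | Chance of at least 36 |
|---|---|---|
| 20% | 36.0 | 59% |
| 22.5% | 34.9 | 42% |
| 25% | 33.75 | 28% |
| 30% | 31.5 | 9% |

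The last column is the exact binomial tail P(X >= 36) with X ~ Bin(45, 1 - attrition), assuming that recruits complete independently. The range of rates allows for the word approximately in the protocol. At exactly 25% the mean shortfall is 36 - 33.75 = 2.25 subjects.

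**3. What a larger cap would do at 25% attrition.** With 48 recruits the chance of at least 36 completers is 58%. With 50 it is 75%, with 52 it is 87% and with 54 it is 94%.

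**4. Effect on power.** Exact two-sample t-test with df = n1 + n2 - 2 and noncentrality 2.1 / (1.7 x sqrt(1/n1 + 1/n2)):

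| Groups compared | Noncentrality | Power at 2.1 | Detectable difference at 80% power |
|---|---|---|---|
| 12 v 12 | 2.1 / 0.694 = 3.03 | 82.4% | 2.03 |
| 12 v 11 | 2.1 / 0.710 = 2.96 | 80.6% | 2.08 |
| 11 v 11 | 2.1 / 0.725 = 2.90 | 78.7% | 2.14 |

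The first row shows that section VI's claim of 80% power at 2.1 is met at 12 per group, with a little to spare. Thirty-four completers split 12/11/11 if balanced. Two of the three pairwise comparisons are then 12 v 11 and stay above 80%. The third is 11 v 11 and falls 1.3 points below.

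**The case against.** Four things can be said for the plan.

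- **The rate is only approximate.** This has some force: at 22.5% the chance of reaching 36 rises to 42%. It does not remove the conflict, because the figures agree only at 20%, which is a stretch for a rate given as about 25% and said to come from experience.
- **The sentence could be read as letting recruitment run until 36 complete, whatever the cap.** The natural reading of an upper limit joined to a completion target is whichever comes first, and nothing in the protocol provides for going past 45. The reading would also leave 45 without a purpose.
- **Power hardly moves.** This stands. A reader might infer that the study would fail to deliver its stated 80% power, but the documents do not support that. On the protocol's own inputs the expected yield leaves power at about 79% to 81% for a difference of 2.1.
- **The losses are benign.** This also largely stands. A reader might take 25% attrition to mean missing outcomes or unequal dropout between groups. The protocol attributes the losses mainly to failing the pain-rating checks, and sections IV and V place randomisation after those checks. The main effect is fewer people randomised, and no bias follows from it.

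**Conclusion.** The recruitment statement is wrong as written, and the error is minor. At the stated attrition, 45 recruits give about 34 completers, and the planned 12 per group is more likely missed (72%) than met (28%), by about two subjects on average. The loss of power is between roughly two points (12 v 12 to 12 v 11) and four points (12 v 12 to 11 v 11), so the stated 80% is essentially intact.

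The probabilities assume independent completion and move with the true rate, as the table shows. The power figures take the SD of 1.7 at face value and on the same scale as the difference of 2.1. The 12/11/11 split assumes balanced allocation.

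**What to change.** Make the figures agree, in one of three ways.

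- **Restate the yield (simplest).** Say in section IV that 45 recruits at about 25% attrition give about 34 completers, or 11 to 12 per group, with power of about 79% to 81% for a difference of 2.1. Align the overview and Session 2 text in section V and the power analysis in section VI. This costs a few edited sentences and no extra subjects.
- **Correct the cap to 48.** State that this gives 36 only on average, with a 58% chance of at least 36. The cost is up to three more people recruited and tested, of whom 3 x 0.75 = 2.25 would be expected to complete. Firmer assurance of 36 would need a higher cap (87% at 52, for example).
- **Correct the attrition figure to 20%.** This is open only if the sponsor's past data support it. Those data are not in the protocol, so the choice cannot be checked here. It changes one figure.

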## **V. STUDY PROCEDURES**

**Overview of Experimental Design**

To accomplish the Specific Aims, a single two-session experiment will be performed with 36 healthy, pain experiment-naïve subjects who will be randomized into 3 treatment groups. The three treatment groups are music conditioning, sound conditioning, and no-treatment routine pain calibration. Primary outcome measures will include the difference (pre- minus post-treatment) in subjective pain rating to calibrated experimental noxious heat stimuli. We will also collect treatment expectations using an Expectancy of Relief Scale (ERS, below) and ratings of subjective responses to treatments assessed through various psychometric scales and surveys for all groups.

The two behavioral sessions will be separated by a minimum of 2 days and a maximum of 10 days. Subjects will be asked to hold common daily activities constant on experiment days (i.e. duration of sleep, eating habits, caffeine intake). Prior to coming to the experimental site, all subjects will be asked to acquire/choose a set of personal music that satisfies certain criteria for the study (see following section). During both sessions, subjects will be receiving sets of calibrated noxious thermal stimuli and after each stimulus will use 0-100 visual analog scales to rate the pain sensation. In the ***first session***, subjects will go through the consent process and screening questions, and we will also determine whether a subject can report consistent, appropriate responses to the application of the calibrated noxious thermal stimuli. This session will last about 120-150 minutes. In the ***second session*** we will repeat testing for appropriate responses to the thermal stimuli – only subjects that perform consistently on the pain rating task (can reliably rate mild intensity pain stimuli as less painful than moderate intensity stimuli and have comparable ratings across sessions - within 1 STD) will continue to further testing during the second session. Subjects who are eligible to continue will be randomized into one of the three treatment groups (N=12/group). These subjects will then receive a modification of a well-characterized conditioning-expectancy manipulation procedure designed to enhance a subject’s expectation of pain relief in response to their assigned treatment. This session will last about 150-180 minutes. At the end of the study all subjects will be de-briefed so that they understand the procedures and why they were used.

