**Session 2: Expectancy manipulation and testing**

Sessions 1 and 2 will be separated by at least two days (but no more than 10 days) to avoid sensitization to repeated application of the noxious stimuli. Before any pain testing begins in Session 2, subjects will complete the STAI-State and BMIS (descriptions below). The rest of Session 2 is made up of **screening/calibration**, **pre-test/baseline, manipulation** and **post-manipulation test**.

The **screening/calibration** block is the same as that completed in Session 1 to determine eligibility to continue participation in the experiment, with this second pass included to thoroughly check for rating consistency (this procedure significantly improves the quality of the data and interpretability of results). The two sets of random stimuli will be applied to regions labeled ‘RS’ in **Figure 2.** If they pass this screening, they will complete a set of **pre-test/baseline** stimuli of the same procedure as the **rating stability testing** from Session 1, though this time in each of regions 1-3 (Figure 2). Ratings for the first set of baseline stimuli during Session 2 must be within 15% of ratings given during rating stability testing during Session 1 to minimize instability of subject rating across sessions. Throughout the administration of noxious pain sequences, subjects will again rate each stimulus using the 0-100 scales immediately after they are presented. After each set of noxious stimuli, subjects will additionally rate their perceived control, valence/arousal, attention, and anxiety.

[figure not shown]

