**Figure 3:**

(Left arm; pink is lower heat, red is higher heat)

After **manipulation** they will again fill out the ERS, and then continue to the **post-manipulation test**. This is the same as **pre-test/baseline,** except that stimuli are now presented in three contexts: their chosen music, their chosen sound, and silence, with order of presentation randomized across subjects. Stimuli are again applied to regions 1-3 on the right arm (Figure2). After each set of audio/silence + noxious stimuli, subjects will additionally rate their perceived control, valence/arousal to the audio or silence, attention, anxiety, and indicate whether any specific memories or autonomic chills responses occurred.

, Subjects will then fill out another ERS indicating their anticipation of their assigned treatment’s analgesic capacity in future treatments, and complete final questionnaires. At this point we may allow subjects to choose either the sound or music sample they listened to previously, and then we will repeat up to two more stimuli blocks with associated ratings identical to those in the post-test. After completion of Session 2 testing procedures, subjects will be debriefed.

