**Data analysis**:
The outcome will be the pain rating differences in different conditions. The data will be analyzed using repeated measures analysis of covariance (ANCOVA) with the corresponding control measures (silence) as the covariate, and conditioning status and audio modality (music and sound) as the factor of interest.

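### The Session 2 pre-test rating enters the primary outcome only by subtraction; naming it as a covariate would be a cheap, though not cost-free, improvement.

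*Protocol*

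**What the plan says.** The overview of the design in section V defines the outcome as a change score: "Primary outcome measures will include the difference (pre- minus post-treatment) in subjective pain rating to calibrated experimental noxious heat stimuli". The Data analysis part of section VI agrees ("The outcome will be the pain rating differences in different conditions") and specifies a "repeated measures analysis of covariance (ANCOVA) with the corresponding control measures (silence) as the covariate", with "conditioning status and audio modality (music and sound) as the factor of interest". The power statement rests on a "two sample t-test at the 0.05 two-tailed significance level", with 12 subjects per group, an SD of the difference of 1.7 and a detectable difference of 2.1.

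In Session 2 the pre-test follows the Session 1 rating-stability procedure (5-6 stimuli at one temperature), "though this time in each of regions 1-3 (Figure 2". The subjects then choose their audio and are randomised. In the post-manipulation test, "stimuli are now presented in three contexts: their chosen music, their chosen sound, and silence", and "Stimuli are again applied to regions 1-3 on the right arm (Figure2". Silence is therefore one of the post-manipulation contexts. Nowhere does the protocol list the pre-test rating as a covariate.

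**The concern.** A raw pre-minus-post difference fixes the slope of the post rating on the pre rating at 1. If the true slope is lower, the difference carries surplus baseline noise, and a group that starts high by chance shows a larger apparent reduction through regression to the mean. Chance imbalance is not negligible with 12 subjects per group, and precision is scarce.

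The pre-test is well suited to adjustment: it is the same measure, in the same regions, taken before randomisation. The silence rating does not stand in for it, because it is taken after randomisation and conditioning.

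**Working it through.** **Inputs from the protocol.** n = 12 per group, difference 2.1, SD of the difference 1.7, two-sided 0.05.

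**Assumptions, since the protocol gives neither.** rho is the pre-post correlation and k is the pre-test SD divided by the post-test SD.

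**1. The plan's own figure.** The non-centrality is 2.1 / (1.7 × √(2/12)) = 3.026. With 22 df and critical value 2.074, power is 82.4%. With n = 11 it is 78.7%. So n = 12 is the smallest group size that reaches 80%, and the stated figure holds.

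**2. Pre-test covariate against the unadjusted t-test.** The residual variance of the difference is multiplied by

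R = (1 - rho²) / (1 + k² - 2 × rho × k), which equals (1 + rho)/2 when k = 1.

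Estimating the slope costs one df (21 remain) and inflates the variance by 1 + 1/20 = 1.05. The non-centrality becomes 3.026 / √(1.05 × R). At k = 1 and rho = 0.5, this is 3.026 / √(1.05 × 0.75) = 3.410.

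| k | rho | R | Power | Change from 82.4% |
|---|---|---|---|---|
| 1 | 0.3 | 0.65 | 93.7% | +11.3 |
| 1 | 0.5 | 0.75 | 90.2% | +7.8 |
| 1 | 0.7 | 0.85 | 86.3% | +3.9 |
| 1 | 0.8 | 0.90 | 84.3% | +1.9 |
| 0.75 | 0.5 | 0.923 | 83.4% | +1.0 |
| 0.5 | 0.5 | 1.00 | 80.4% | -2.0 |

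**3. Pre-test covariate added to a silence-adjusted model.** The planned model is not unadjusted, so this comparison matters more. Take k = 1 and all correlations equal to rho. Two covariates leave 20 df and inflate the variance by 1 + 2/19.

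*Silence as a change score sharing one pre-test mean.* The two change scores have covariance proportional to 1 - rho and variance proportional to 2(1 - rho), so they correlate at 0.5. Silence alone then gives R = 1 - 0.25 = 0.75 and power 90.2% at every rho. With the pre-test added, R = (1 + 2 × rho) / (2 × (1 + rho)).

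| rho | R with pre-test | Power | Change from 90.2% |
|---|---|---|---|
| 0.3 | 0.615 | 93.7% | +3.5 |
| 0.5 | 0.667 | 91.8% | +1.6 |
| 0.7 | 0.706 | 90.3% | +0.1 |
| 0.8 | 0.722 | 89.6% | -0.5 |

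With a narrower pre-test spread and rho = 0.5, power moves from 86.2% to 85.6% (k = 0.75) or from 84.8% to 82.7% (k = 0.5).

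*Silence as the post-manipulation rating itself.* With equal correlations it is uncorrelated with the change score, since the covariance is rho - rho = 0. It gains nothing and costs one df (80.4%). At rho = 0.7, adding the pre-test gives R = 0.706 and power 90.3%, about +10 points.

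*Silence as a change score with region-specific pre-tests.* The covariance is again 0, so silence alone gives 80.4%. At rho = 0.7, adding the matching pre-test gives R = 0.85 and power of about 84%, about +4 points.

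**4. Conditional bias.** Given a pre-test imbalance between two groups, the change-score contrast is shifted by (1 - slope) × imbalance. With k = 1 and rho = 0.5, the SD of the difference equals the SD of a single rating, 1.7. One standard error of imbalance is 1.7 × √(2/12) = 0.69, and the shift is 0.5 × 0.69 = 0.35. That is about one sixth of the 2.1 the trial is sized to detect.

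**The case against.** **The covariate list may belong to the SAP.** The Data analysis section is two sentences long and does not say that silence is the only covariate. This has some weight. But the section does state the outcome, the model, a covariate and the factors, and the covariate it chose is not the baseline.

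**Nothing stated is invalid.** This stands. Under randomisation a change score is unbiased on average and has valid type I error. The bias described above is conditional on the imbalance that happens to occur. A reader might infer that the planned analysis is biased or wrong; the documents do not support that. The plan also meets its own 80% target.

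**The t-test is the wrong comparator.** This also stands. The protocol uses the t-test only for sizing. A reader might take the gain of about 8 points at rho = 0.5 as the expected benefit, but part 3 of the working shows that it can shrink to almost nothing, depending on how the silence covariate is defined. The protocol does not settle that definition.

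**Equal SDs may be optimistic.** Temperatures are set individually to reach each subject's lower Strong ratings, which may narrow the pre-test spread. The 15% rule probably matters less: it compares the first baseline set with the subject's own Session 1 ratings, so it mainly limits drift within a subject.

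**Adjustment is not free.** A reader might infer that it costs nothing because the data are already collected. It uses one df and an estimated slope, and it loses about 2 points of power in the worst case tried.

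**Conclusion.** The point holds as a recommendation to improve the analysis, not as an error in the plan. The protocol fixes a pre-minus-post outcome and names only a post-manipulation measure as covariate, so a suitable pre-randomisation baseline is used with a forced slope of 1. Adjusting for it removes the conditional bias and usually improves precision.

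The size cannot be fixed from the documents. In the cases tried it runs from about +11 points of power (unadjusted comparator, equal SDs, rho 0.3) to about -2 points (pre-test SD half the post-test SD, rho 0.5). All the powers take the protocol's 1.7 and 2.1 at face value and refer to a single pairwise contrast. Whether that SD suits a 0-100 scale was not examined.

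**What to change.** In section VI, state that the model for each primary contrast includes the Session 2 pre-test rating as a prespecified covariate, either from the matching skin region or as the subject's mean over regions 1-3, and say which. Keep randomised group and audio context as the factors. The outcome may be the post-manipulation rating or the pre-minus-post difference: with the same pre-test rating as covariate, the group contrast is identical. Report the unadjusted pre-minus-post difference as a sensitivity analysis. In the same place, state whether the silence covariate is a rating or a change score, because the gain depends on it.

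The cost is one or two sentences, with no new data, visits or subjects. The statistical price is one degree of freedom and an estimated slope, at most about 2 points of power in the cases tried.
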